#### Study research design

This study is a four-arm cluster randomized trial that has two interventions: a community stigma awareness workshop (for communities) and the CHC+ (for couples). Specifically, 24 Cape Town communities located near clinics that provide ART and PrEP were randomized into one of four arms (see **Fig 3**): (1) stigma awareness workshop (community) and HTS/PrEP/ART (couples); (2) stigma awareness workshop (community), and HTS/PrEP/ART with the CHC+ (couples); (3) no stigma awareness workshop (community) and HTS/PrEP/ART (couples; control); and (4) no stigma awareness workshop (community), and HTS/PrEP/ART with the CHC+ (couples). Twenty couples (a total of 480 couples), defined as young women and their primary male partners both aged 18 to 30 are recruited from each community. Depending on the study arm of their community, couples are provided with HTS/PrEP/ART and/or the CHC+. Couples are asked to return for two study follow-up appointments at 3- and 6-months post-enrollment. Communities are already assigned to receive either the stigma awareness workshop or no workshop, with baseline and repeated follow-up surveys with community members. Recruitment began in July 5, 2022 and is ongoing.

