#### Sample size

A sample size of 480 couples, 120 per each of the four study arms, was chosen to ensure sufficient statistical power to detect meaningful differences in our primary outcomes of couple-level ART/PrEP initiation and adherence between intervention and control groups. These power calculations assume 80% power, and an intraclass correlation coefficient (ICC) of 0.05 (based on the team’s previous R01 study with couples in Cape Town) [22], with an estimated follow-up of 95% at 3-month follow-up and 90% at 6-month follow-up. On average, a sample size of 97 community members in each of the 24 catchment areas was calculated to detect a 10% difference between control and intervention conditions on measures of stigma reduction. Using a two-sided chi-square test of proportions with a significance level of 0.05 and nested design model with additivity on the primary intervention effect (stigma awareness community workshop as compared with no community workshop) and secondary intervention effect (CHC+ as compared with HTS), our sample size was selected to ensure power for contrasts based on the presence of an interaction between the community-based stigma awareness workshop and the CHC+. For a hypothesis related to ART/PrEP initiation among couples in the CHC+ arm as compared with couples in the HTS arm, we will be able to detect a minimal effect size of 0.23. The minimal effect size of the CHC+ intervention on ART/PrEP adherence by couples in the CHC+ arm at 6 months is estimated to be 0.34 compared with couples in clinics in the HTS arm. For the evaluation of the efficacy of the stigma awareness workshop plus the CHC+ as compared with no stigma awareness workshop plus HTS (control), the minimal effect size related to ART/PrEP initiation is estimated to be 0.45. For examination of the intervention components’ effects (stigma awareness workshop and the CHC+) on ART/PrEP adherence), the minimal effect size is estimated to be between 0.26 and 0.6 for retention at 3-month and 6-month follow-up.

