Reduction in stigmatizing attitudes and behaviors toward young women and men who use AODs and other people seeking HIV services and other health services.	**Community Stigma Awareness**: Surveys measure stigmatizing attitudes and beliefs toward people who use AODs, people living with HIV and seeking ART, and people seeking PrEP services for prevention. Greater values indicate higher levels of community-level stigma and discrimination.	Baseline, 4 months, and 8 months
Reduced observations of HIV status and AOD use related stigma perpetrated by the community.	**Self-report:** Participant observed or experienced stigma perpetrated by members of their community as measured by the PRBA+.	Baseline, 3 months, and 6 months follow-up (FU)
**Aim 3: Reduce alcohol and other drug use, sexual risk and gender-based violence, and enhance positive gender norms and communication relative to HIV testing services.**		
Reduction in recent drug use (amphetamine, cocaine, methamphetamine, marijuana [THC], opiates and/or Mandrax).	**Biological:** Measured using a rapid urine-based drug screening test panel. **Self-report:** ASSIST frequency of use and RRBA injection use.	Baseline, 3 months, and 6 months FU
Reduction in recent alcohol use.	**Biological:** Measured by the presence of ethyl glucuronide (EtG), a breakdown product of ethanol, using an EtG urine test. Alcohol urine tests measure past 10 days of use. **Self-report:** Consumption days, problematic drinking days (4+ for women; 5+ men), combining alcohol with other drugs.	Baseline, 3 months, 6 months FU
Reduction in gender-based violence. FG	**Self-report:** Relationship violence, physical abuse, sexual abuse, and recent victimization measured by modified World Health Organization and RRBA items.	Baseline, 3 months, and 6 months FU
Reduction in sexual risk: Increased condom and contraception use, decreased number of partners or concurrent partners, decrease in impaired sexual encounters.	**Self-report:** Last sex condom use, number of sex partners, concurrent sexual partners and sex trading partners, AOD use prior to sex, and use and types of contraception asF measured by the PRBA+.	Baseline, 3 months, and 6 months FU
Greater equity in traditional attitudes about gender roles, empowerment, and assertiveness;	**Self-report:** Attitudes about traditional gender roles, empowerment and assertiveness will be measured by the GIS and the PRBA+.	Baseline, 3 months, and 6 months FU

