### Statistical analysis plan and hypotheses

We will examine the distribution, frequency, and missing values in each variable using frequency tables for categorical variables and univariate distributions for continuous variables. We will compare data across the arms to examine the balance of baseline demographic and clinic characteristics using chi-square tests and t-tests or their nonparametric alternatives, as appropriate. Next, we will examine the association between demographics, clinic characteristics, primary outcomes, and any important mediators and moderators to determine which variables will be entered in the generalized linear models (GLM). We will use a GLM with generalized estimating equations (GEE) to test the relative efficacy of the interventions on the primary outcomes. GEE allows one to adjust for clustering and accommodates multiple types of outcomes (dichotomous, continuous, ordinal) and dyadic data analysis. We will use the couple as the unit of analysis for ART/PrEP initiation and adherence. First, we will fit a logit model that regresses the dependent variable on the membership in the arms and visit, and an interaction between visit and arm. Second, if descriptive analysis suggests there are significant differences in demographics or characteristics of clinics across the arms, those variables will be added into the model as covariates. We will test ART/PrEP initiation and adherence across two arms at a time by estimating contrasts at each time point to test both the hypotheses that the CHC+ increases ART/PrEP initiation and adherence. We will use an identical process to estimate the impact of the interventions on AOD use, GBV, sexual risk-taking, communication, and gender norms. The distribution in the GLM will be modified to be multinomial for ordinal outcomes, binary for dichotomous outcomes, and continuous or Poisson for continuous or count outcomes, respectively. The unit of analysis for outcomes (e.g., condomless sex) will be at the couple level and/or individual level, when appropriate, which the study team has done in previous couples-based analyses [15]. Analyses will be performed for the 3-month and 6-month follow-up time periods to determine if there are differential effects over time on ART/PrEP initiation and adherence, and at the 6-month time period for secondary outcomes.

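### Secondary outcomes are measured at baseline, but neither the baseline value nor the randomisation stratum is a prespecified covariate, which gives up precision at 6 months

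*Protocol article*

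**What the plan says.** All of the analysis text is in the section Statistical analysis plan and hypotheses of the protocol article.

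- **Model.** A GEE that "regresses the dependent variable on the membership in the arms and visit, and an interaction between visit and arm". For ART/PrEP initiation and adherence, two arms at a time are compared by "estimating contrasts at each time point".
- **Extension to secondary outcomes.** "We will use an identical process to estimate the impact of the interventions on AOD use, GBV, sexual risk-taking, communication, and gender norms".
- **Covariates.** The second modelling step acts on "significant differences in demographics or characteristics of clinics across the arms, those variables will be added into the model as covariates". An earlier screening step looks at associations among demographics, clinic characteristics, primary outcomes, mediators and moderators to decide what enters. Neither step names the baseline value of a secondary outcome.
- **Timing.** ART/PrEP results are analysed at 3 and 6 months, and the rest "at the 6-month time period for secondary outcomes".
- **Data collected.** Table 3 (Overall study measures) schedules drug use, alcohol use, gender-based violence, sexual risk, gender attitudes and partner communication at "Baseline, 3 months, and 6 months FU", with minor variation in wording.
- **Randomisation.** Communities were randomised within three population-group strata of eight. The stated model has no stratum term.

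**The concern.** Table 3 frames these outcomes as reductions or increases, and each has a baseline measurement. Such behaviours tend to persist within a person or couple, so the baseline value is likely to predict the 6-month value. With 6 communities per arm, baseline levels can also differ between arms by chance.

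The covariate rule does not reliably deal with this. It looks at demographics and clinic characteristics, not at baseline outcomes, and it acts only on a significant difference. It is also unlikely to bring in the stratum, because allocation was balanced within strata by design. At stake is how precisely the trial can estimate effects on alcohol and drug use, violence, sexual risk, gender norms and communication. The primary ART/PrEP outcomes are not affected.

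**Working it through.** **Inputs from the article.** "A sample size of 480 couples, 120 per each of the four study arms"; 24 communities of 20 couples; ICC 0.05; 80% power; two-sided 0.05; 90% follow-up at 6 months. CHC+ against HTS compares 12 with 12 communities, or 240 with 240 couples. At 90% follow-up that is 216 with 216, or 18 couples per community.

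**Assumed.** The baseline-to-6-month correlation r is not given. I take 0.3 to 0.7 and the same value at couple and community level.

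**The plan's own figure.** No detectable difference is stated for any secondary outcome. The nearest is 0.34 for adherence at 6 months. The inputs above give 0.367 (below), or 0.325 one-sided, so 0.34 is not reproduced. Its effect-size metric is undefined, so I do not call it wrong, and nothing here depends on it.

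**Step 1: does including baseline as a visit adjust the 6-month contrast?** With arm, visit and arm by visit, the mean model has a free mean for every arm at every visit. With complete data the fitted 6-month contrast should therefore equal the raw 6-month difference. A GEE fitted to simulated data (24 communities of 20) confirms this:

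| Data | Scale | GEE contrast | Raw difference |
|---|---|---|---|
| Complete | Linear | 0.00157 | 0.00157 |
| Complete | Logit | -0.11675 | -0.11675 |
| 5% missing at 3 months, 10% at 6 months | Linear | -0.070 | -0.089 |
| 5% missing at 3 months, 10% at 6 months | Logit | -0.034 | -0.038 |

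The other visits matter only through missing data. The contrast is essentially unadjusted.

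**Step 2: would a change-from-baseline contrast do as well?** Relative to the unadjusted contrast, with equal variances at both visits, the variance factor is 2(1 - r) for a change score and 1 - r² for baseline adjustment. The gap is 2(1 - r) - (1 - r²) = (1 - r)², which is never negative. At r = 0.3, 0.5 and 0.7 the change score gives 1.40, 1.00 and 0.60, against 0.91, 0.75 and 0.51.

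**Step 3: unadjusted detectable difference, 12 v 12 communities.**

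- Design effect = 1 + (18 - 1) × 0.05 = 1.85
- Detectable difference = (1.960 + 0.842) × sqrt(2 × 1.85 / 216) = 2.802 × 0.1309 = 0.367 SD

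**Step 4: with baseline adjustment**, 0.367 × sqrt(1 - r²):

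| r | Variance factor | Detectable difference (SD) | Power at 0.367 SD | Equivalent extra couples, 1/(1 - r²) - 1 |
|---|---|---|---|---|
| 0 (unadjusted) | 1.00 | 0.367 | 80% | 0% |
| 0.3 | 0.91 | 0.350 | 83.6% | 10% |
| 0.5 | 0.75 | 0.318 | 89.9% | 33% |
| 0.7 | 0.51 | 0.262 | 97.5% | 96% |

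At r = 0.2 the variance falls by only 4%.

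**Step 5: two single arms (6 v 6 communities, 108 v 108 couples).** 2.802 × sqrt(2 × 1.85 / 108) = 0.519 SD. Multiplying by the same factors gives about 0.49, 0.45 and 0.37.

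**Step 6: simulation check.** With community effects that stay constant over time, baseline adjustment reduced the variance to 0.73, 0.52 and 0.32 of the unadjusted value for a continuous outcome. For a binary outcome (risk difference, correlation on the latent scale) it fell to 0.84, 0.73 and 0.57. The gain is therefore not confined to continuous outcomes.

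**The case against.** The strongest reply is that this is a condensed article, that final covariates normally belong in an analysis plan not shown here, and that the screening step leaves the covariate list open. That would answer a complaint of missing detail. The article, however, states the model terms and the covariate rule itself, and on those terms the baseline outcome is at best a variable that screening might admit.

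Four stronger readings are tempting, and the documents do not support them.

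- **The plan never adjusts for baseline on any reading.** The article does not say whether baseline counts as a visit. The sentence on contrasts at each time point is about ART/PrEP; applying it to outcomes with a baseline value is an inference from the identical-process wording. If the authors meant arm by visit as a difference in change, baseline does enter and chance imbalance is removed. Step 2 shows only that this is no more precise than covariate adjustment.
- **The 3-month data play no part.** A model with visit terms holds more than one visit, and step 1 shows that other visits can move the 6-month estimate when data are missing.
- **The timing sentences contradict each other.** The last sentence can be read as setting scope: 3 and 6 months for ART/PrEP, 6 months for the rest. A single main time point for many secondary outcomes is sensible.
- **The results will be biased.** Nothing shown here is bias from the model.

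Two limits raised against the point also stand. The size rests on an assumed correlation, and the range is wide. And both partners must report weekly alcohol or drug use and recent condomless sex at entry, so yes/no versions of those items hardly vary at baseline and gain little.

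**Conclusion.** The point holds as an avoidable loss of precision on secondary outcomes. As written, neither the baseline value nor the stratum is prespecified. Both plausible readings of the contrast (difference at 6 months, or difference in change) are no more precise than adjusting for baseline.

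For 12 against 12 communities, with ICC 0.05 and 90% follow-up, the variance reduction forgone is about 9%, 25% or 49% at assumed correlations of 0.3, 0.5 or 0.7. The figures use normal quantiles and a common correlation at couple and community level, and they credit nothing to the stratum term. They apply to frequency measures, urine screens, violence, partner numbers and scales rather than to the near-constant yes/no entry items. The change is worth making because it uses data already scheduled.

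**What to change.** For each secondary outcome measured at baseline, prespecify one GEE on the 3- and 6-month visits with these terms:

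- arm, visit and arm by visit;
- the baseline value of that outcome;
- the population-group stratum.

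Include the last two whatever imbalance is observed. Keep the 6-month contrast as the main one and report 3 months as supportive. For binary outcomes, report a marginal (standardised) effect, because conditioning on baseline changes the odds ratio being estimated. State in the text that baseline enters as a covariate and not as a visit.

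The cost is a change of wording and slightly more analysis and reporting work. No new data are required.

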### Data and safety monitoring plan

To prioritize confidentiality, each participant in the study is assigned a unique alphanumeric study participant identification number (PID), which serves as the sole link between the behavioral and biological data and the identifying information collected. Safeguarding the privacy of participants is of utmost importance. Data collected through ACASI are transmitted securely to a central server at RTI International in the USA. Personally identifiable information (PII) is stored separately and is accessible only to authorized study staff. To ensure the highest level of security, deidentified DBS samples are stored and shipped for analysis to certified laboratories that adhere to strict data management protocols, maintaining confidentiality and complying with ethical standards. The data collection process is carried out by highly trained staff from the local community, who establish rapport with the study participants to foster trust and obtain the most accurate data possible. All staff members sign confidentiality agreements and undergo comprehensive training on the study’s Quality Assurance Protocol and Quality Management Plan (QMP). A robust quality assurance plan has been developed and regular process monitoring at each step is conducted to review files and ensure fidelity of each intervention. Training is conducted on the manualized field procedures and a post training manual test and regular booster training are also conducted. To maintain oversight and ensure efficient operations, the Multiple Principal Investigators, other members of the research team, and the field staff receive daily field activity reports. This allows for continuous monitoring of progress and facilitates prompt attention to any issues that may arise.

#### Reporting of adverse events

Procedures have been put in place to address adverse events (AEs) or serious adverse events (SAEs), such as improper disclosure of information or mental or emotional discomfort, respectively. As specified in our Data and Safety Monitoring Plan (DSMP), SAEs are reported immediately to the South African Multiple Principal Investigator or Medical Director, who will contact the US-based Contact Principal Investigator. Based on advice from the aforementioned project staff, the field staff will make appropriate referrals to medical, counseling, and/or other health services. SAEs and Incident Reports will be reviewed immediately. SAEs will be reported within 24 hours of their occurrence by the Principal Investigator to the Project Officer, ethics committee, and the Chair of the Data and Safety Monitoring Board (DSMB). A DSMP ensures that procedures have been set in place to safeguard the security, validity, and integrity of study data, and that study staff are trained on the policies and procedures for data management according to the Quality Assurance Protocol. The DSMP also outlines the data analysis plan, including preliminary analyses of data for quality assurance and to track the progress of the study.

### Dissemination plan

The study findings will be disseminated to communities and stakeholders through the PAB, CCB, program newsletters, peer-reviewed journal articles, conference presentations, and targeted channels. This study team also has had success in conducting policy and impact forums with community members and the government to further disseminate study findings. This forum will provide the opportunity for conversation with South African government officials on how this intervention could be scaled up.

### Protocol amendments

The study adheres to ethical guidelines, obtains informed consent, maintains participant confidentiality, and provides referrals for necessary support services. All study activities have been reviewed and approved by relevant ethical review boards. Since receiving approval to conduct the randomized trial, we amended the protocol to improve the study design and procedure.

As the study was delayed in the initial commencement of the trial, we removed the 12-month follow-up, prior to the experimental phase. We also removed the 9-month follow-up after the trial commenced because of timeline concerns related to social unrest in the study communities.

## Discussion

South Africa faces numerous challenges, with disruptions in electricity, water shortages, ongoing strikes, and violence. Since the beginning of the COVID-19 pandemic, healthcare providers have been stretched and in 2024 public health services budgets have also been cut, further challenging the most economically disadvantaged communities and key populations in receiving necessary services. Community factors—including high rates of poverty and people’s continued use of AODs, which also intersect with condomless sexual risk behavior, gender-based violence, and the high burden of HIV among young women and their partners—reinforce the need for working with young couples and within their communities. This protocol describes the Couples Health CoOp Plus (CHC+) study, which aims to address these intersecting epidemics by integrating ART/PrEP initiation and adherence within the existing CHC model and by conducting community stigma awareness workshops. By adopting a multilevel social ecological framework, the study seeks to enhance HIV prevention efforts, improve treatment outcomes, and alleviate the burden of HIV in this key population and raise community sensitivity. The study findings have the potential to guide future interventions and contribute to ending the HIV epidemic in South Africa.

## Abbreviations

ACASI: audio computer-assisted self-interviewing
ART: antiretroviral therapy
ASSIST: Alcohol, Smoking and Substance Involvement Screening Test
CCB: Community Collaborative Board
DBS: dried blood spots
DSMP: Data and Safety Monitoring Plan
ETG: ethyl glucuronide
FTC-TP: FTC Triphosphate
HTS: HIV testing services
PAB: peer advisory board
PII: personally identifiable information
PrEP: Pre-exposure prophylaxis
QMP: quality management plan
RRBA: Revised Risk Behavior Assessment
SAE: serious adverse event
SRH: sexual and reproductive health
STD or STI: sexually transmitted disease or infection
